## Abstract

**Background:**

Aortic stenosis (AS) is common in patients on dialysis as well as in the general population. AS leads to difficulty with dialysis therapy because of unstable conditions such as intradialytic hypotension due to low cardiac output. However, the precise morbidity rates and risk factors of AS in patients on dialysis are unknown. Moreover, there are no large-scale observational studies regarding the association between AS in patients on dialysis and mortality. Therefore, we will investigate whether morbidity of AS in patients on dialysis is associated with mortality.

**Methods:**

This is a multicenter prospective cohort analysis in the Tokai region of Japan. The 75 participating centers in this study will enroll approximately 2400 patients during 12 months, with or without AS. We started enrollment in July 2017 and will follow patents until June 2023. Transthoracic echocardiography will be performed to evaluate aortic valve. Parameters used for evaluation of aortic valve are mean pressure gradient between left ventricle and ascending aorta, aortic valve area, and maximum aortic jet velocity. We will diagnose AS using the criteria based on the 2014 American Heart Association/ American College of Cardiology Guideline. We will also perform transthoracic echocardiography at 12, 24, 36, 48, and 60 months. Survival prognosis and CV events will be determined at the end of June 2019, 2020, 2021, 2022, and 2023. Development of AS will be also evaluated as new onset or annual change in AS parameters. We will classify patients based on the presence or absence of AS and the stages of AS and will compare outcomes. Study outcomes will include the following: 1) all-cause mortality rates; 2) incidence of cardiovascular (CV) events; 3) CV-related mortality rates; 4) infection-related mortality rates; 5) new onset or development of AS.

**Discussion:**

We will consider the following hypotheses in this study, among others: The prevalence of AS is higher in dialysis patients; new onset and development of AS are associated with factors that are specific for dialysis, such as hyperphosphatemia, hyperparathyroidism, and medication; and outcomes in AS patients are poorer than in patients without AS at baseline.

**Trial registration:**

UMIN000026756, Registered March 29 2017.

## Backgrounds

The number of patients on maintenance dialysis is increasing worldwide. Diabetic nephropathy and hypertensive kidney disease account for most of these patients. Chronic kidney disease (CKD) is an independent risk factor for cardiovascular disease (CVD) [1–5]. Moreover, CVD, which leads to difficulty with dialysis therapy, is strongly associated with higher mortality. Coronary heart disease is a typical condition among CVDs. However, aortic stenosis (AS) is increasingly frequent in patients on dialysis. Previous reports have indicated that onset and progression of AS were related to aging, hypertension, diabetes, or lipid disorders [6–8]. Some epidemiological studies in the general population have shown that the morbidity rate of AS in those over 75 years old is 2–4% [9]. Another general population study involving over 1.2 million individuals in Canada revealed that there were 20,995 patients who needed admission to hospitals or interventions for AS during 13 years of median follow-up [10]. On the other hand, patients on dialysis are more likely to develop AS because of hyperphosphatemia, anemia, and other factors. However, accurate morbidity rates and risk factors of AS in patients on dialysis remain unknown. Moreover, there are no large-scale observational studies of the association between AS in patients on dialysis and mortality or onset of cardiovascular (CV) events. Hence, we will examine whether morbidity of AS in patients on dialysis is associated with mortality, using the database of the Tokai Aortic Stenosis Cohort in Patients on Dialysis. We believe this is the first study to evaluate this association. We will consider the following hypotheses in this study: 1) The prevalence of AS is higher in dialysis patients than in the general population. 2) New onset and development of AS are associated with traditional risk factors including aging and comorbidity of diabetes. 3) New onset and development of AS are associated with factors that are specific for dialysis such as hyperphosphatemia, hypercalcemia, and hyperparathyroidism. 4) Outcomes in AS patients are poorer than in patients without AS at baseline. 5) Outcomes are poorer according to AS stages.

## Methods/design

### Subjects

The study is a multicenter, prospective cohort analysis in the Tokai region of Japan (Tokai Aortic Stenosis Cohort in Patients on Dialysis). We started enrollment in July 2017. The 75 participating centers in this study will enroll approximately 2400 patients during 12 months. Whether or not AS is present, we will include outpatients who are on maintenance dialysis for at least 12 months, aged over 20 years old, who undergo echocardiography every year, and agree with participation in this study.

### Patient characteristics and data at the time of enrollment (baseline)

Baseline is defined as the time at which echocardiography is performed for the first time from July 2017 to June 2018. We will review the following: 1) age, sex, dialysis vintage, and original kidney disease, blood pressure, and resting heart rate; 2) comorbidities including diabetes mellitus and malignancy; 3) medical history including hospitalization because of heart failure within one year, coronary heart disease, aortic disease, stroke, peripheral artery disease, malignancy, and history of parathyroidectomy; 4) medication including renin-angiotensin blockers, calcium channel blockers, β blockers, vitamin D receptor activators, calcimimetics, phosphate binders, and warfarin; 5) laboratory data including hemoglobin, platelet count, and serum albumin, alkaline phosphatase, uric acid, urea nitrogen, creatinine, adjusted calcium, phosphorus, magnesium, intact parathyroid hormone (PTH), ferritin, and C-reactive protein levels.

### Echocardiography measurements

Transthoracic echocardiography will be performed by using commercially available ultrasound systems owned by each facility during enrollment and the follow-up period every year by an experienced technician. All parameters will be assessed with B mode or tissue Doppler imaging. The investigator will be blinded to clinical data. Findings will be confirmed by a cardiologist. The parameters used for evaluation of aortic valve are mean pressure gradient (mPG) between left ventricle and ascending aorta, aortic valve area (AVA), and maximum aortic jet velocity (aortic Vmax). Doppler echocardiographic measurements will include the peak and transaortic mPG using the simplified Bernoulli equation, and the AVA using the standard continuity equation or planimetry method in most participating facilities. Continuous wave Doppler will be used at multiple windows to obtain the maximal jet velocity over the aortic valve as well. In addition to the AS parameters, we will measure various parameters including left ventricular ejection fraction, left ventricular mass index, left atrial diameter, and E/E’. We will also examine aortic valve calcification.

### Definition and classification of AS

We will diagnose AS using the following criteria based on the 2014 American Heart Association/ American College of Cardiology (AHA/ACC) Guideline for the Management of Patients with Valvular Heart Disease: 1) mPG > 20 mmHg, or 2) AVA < 1.0 cm2, or 3) aortic Vmax > 2.0 m/s [11]. We will evaluate stages A to D of AS according to the AHA/ACC Guideline. We will compare patient profiles, laboratory data at baseline, and outcomes including all-cause mortality and CV events among patients 1) with or without AS, and 2) 4 groups by stages.

### Follow-up schedule

Table 1 shows the follow-up schedule. According to baseline characteristics and laboratory data, we will examine variables, which include comorbidities and medication at 12, 24, 36, 48, and 60 weeks. We will also perform transthoracic echocardiography at 12, 24, 36, 48, and 60 months. Survival prognosis and CV events will be determined by sending letters to facilities at the end of June 2019, 2020, 2021, 2022, and 2023. These letters include a questionnaire regarding the categories of CV events, date of onset, and clinical outcomes.

**Table 1 Tab1:** Research Schedule

Date	Contents
July 1, 2017 – June 30, 2018	Case registration
September 30, 2017	Fixation of baseline data
	Preparation of paper on baseline
July 1, 2018 – June 30, 2023	Transthoracic echocardiography examination every year
	Surveillance of outcomes every year
December 31, 2023	Fixation of final data
January 1, 2024 –	Preparation of papers on outcomes
	Presentation at relevant national and international conferences

### Outcomes

Study outcomes will include the following: 1) all-cause mortality rates, 2) incidence of CV events, 3) CV-related mortality rates, 4) infection-related mortality rates, and 5) new onset or development of AS. CV events are defined as heart failure requiring hospitalization, acute coronary syndrome, coronary artery disease requiring percutaneous coronary intervention, coronary artery bypass grafting, or medication, and stroke or peripheral artery disease requiring hospitalization. CV-related death is defined as death due to heart failure, acute coronary syndrome, aortic disease, or stroke. Infection-related death includes sepsis associated with peripheral artery disease. Development of AS is evaluated as new onset of AS or annual change in mPG, AVA, and aortic Vmax.

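### The closed definition of CV-related death has no place for sudden or arrhythmic death, or for death from valve disease or a valve procedure, although aortic stenosis is the exposure

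*Protocol article*

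**What the plan says.** The Outcomes section of the protocol article lists five outcomes: "1) all-cause mortality rates, 2) incidence of CV events, 3) CV-related mortality rates, 4) infection-related mortality rates, and 5) new onset or development of AS". It then defines the second, third and fourth.

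- **CV events:** "CV events are defined as heart failure requiring hospitalization, acute coronary syndrome, coronary artery disease requiring percutaneous coronary intervention, coronary artery bypass grafting, or medication". The last item on this list is "stroke or peripheral artery disease requiring hospitalization".
- **CV-related death:** "CV-related death is defined as death due to heart failure, acute coronary syndrome, aortic disease, or stroke".
- **Infection-related death:** "Infection-related death includes sepsis associated with peripheral artery disease".

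The baseline section collects a history of "coronary heart disease, aortic disease, stroke, peripheral artery disease, malignancy". Aortic disease is thus a history item of its own, and the article does not say whether it covers the aortic valve.

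Under Statistical processing, each outcome is analysed separately by Kaplan-Meier curves with the log-rank test and by Cox regression. Under Follow-up schedule, events are collected by yearly letters to the facilities, with a questionnaire on event category, onset date and clinical outcome.

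**The concern.** The study asks whether AS worsens prognosis in dialysis patients (hypotheses 4 and 5 in the Backgrounds section). CV mortality is the cause-specific outcome closest to that question. A death from the stenotic valve, from its replacement, or of sudden or arrhythmic type has no clear home in the definition. The article itself makes valve procedures relevant: its section on treatment strategy discusses surgical and transcatheter replacement and notes that treatment-related mortality has been higher in dialysis patients.

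Three things are at stake. CV mortality would be understated. The analysis would have fewer events. The 75 centers could code the same valve death differently, some under heart failure, some under aortic disease and some under neither.

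**Working it through.** **No figure to reproduce.** The Sample size section gives only an expected enrollment of over 2400. It states no event rate, effect size or power. The check is therefore a comparison of the lists, followed by illustrations on assumed rates.

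**1. The lists side by side**

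| Cause | CV event | CV death |
|---|---|---|
| Heart failure | if hospitalized | yes |
| Acute coronary syndrome | yes, no admission condition | yes |
| Other treated coronary disease | yes | no |
| Stroke | yes (admission condition may or may not apply) | yes |
| Peripheral artery disease | if hospitalized | no (related sepsis goes to infection) |
| Aortic disease | no | yes |
| Sudden or arrhythmic death | no | no |
| Valve disease or valve procedure | no | not named |

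The CV-death sentence defines by enumeration. The infection sentence uses inclusive wording and so is open. Only the first shuts out unlisted causes.

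If aortic disease is read narrowly (the vessel), valve deaths are excluded. If it is read broadly, some valve deaths enter, procedure deaths remain uncertain, and sudden death is excluded on either reading.

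**2. Effect on the CV-death rate and hazard ratio.** Assumed true CV death rates are 6.0 (AS) and 3.0 (no AS) per 100 person-years, a ratio of 2.0. Recorded rate = true rate × (1 − omitted share).

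| Omitted share, AS / no AS | Recorded rates | Recorded ratio |
|---|---|---|
| 1/3 and 1/4 | 6.0 × 2/3 = 4.0; 3.0 × 3/4 = 2.25 | 4.0/2.25 = 1.78 |
| 1/3 and 1/3 | 6.0 × 2/3 = 4.0; 3.0 × 2/3 = 2.0 | 4.0/2.0 = 2.0 |
| 1/4 and 1/3 | 6.0 × 3/4 = 4.5; 3.0 × 2/3 = 2.0 | 4.5/2.0 = 2.25 |

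Rates are too low by the omitted share in every row. In the middle row the omitted deaths are twice as frequent with AS (2.0 against 1.0 per 100 person-years), yet the ratio does not move. What matters is the share of CV deaths, not the frequency of the omitted ones.

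**3. Loss of events.** From the documents: N = 2400 and a 5% significance level. Assumed: a two-sided test, 20% with AS, five years, CV death 3% per year without AS, other death 4% per year in both groups, and a hazard ratio of 1.5 for every CV cause.

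Expected CV deaths per patient = (CV rate / total rate) × (1 − exp(−5 × total rate)).

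- No AS: 1920 × (0.03/0.07) × (1 − exp(−0.35)) = 243
- AS: 480 × (0.045/0.085) × (1 − exp(−0.425)) = 88
- Total: 331

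With 10% to 30% of CV deaths unlisted, 0.9 × 331 = 298 down to 0.7 × 331 = 232 are captured. Power by the Schoenfeld formula, Φ(√(D × 0.2 × 0.8) × ln 1.5 − 1.96), is 0.84 for 331 deaths, 0.80 for 298 and 0.70 for 232.

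**4. If unlisted causes are more strongly related to AS.** Keep 1.5 for listed causes and assume 3.0 for unlisted ones. With s the unlisted share of CV deaths without AS, the ratio for all CV deaths is (1 − s) × 1.5 + s × 3.0. This is 1.65 at s = 0.1 and 1.95 at s = 0.3, while the closed list still estimates 1.5.

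**The case against.** The strongest reply is that the main question is untouched. All-cause mortality is listed first and captures every death, and the article makes no power claim that lost events could undermine. This stands, and it limits the point to a cause-specific outcome.

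A reader might infer that fatal CV outcomes of AS are lost altogether. They are not. A valve death attributed to heart failure counts as CV death. Fatal acute coronary syndrome is both a CV event and a CV death. A patient with an earlier qualifying event already has a CV event.

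A reader might also infer bias toward no difference on both CV endpoints. The documents do not support that. For CV death the direction depends on cause-of-death shares that they do not give. For CV events nothing can be computed from them. That such patients would be censored at death is an inference from the planned Kaplan-Meier and Cox analyses. The article states no rule, and one may stand in an analysis plan that is not shown.

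Finally, the two lists need not nest. Keeping a morbidity endpoint apart from a mortality endpoint is a legitimate design, and placing sepsis with peripheral artery disease under infection is evidently deliberate.

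What does not fall to these replies is the closed list itself. The article states it outright, so this is not detail merely left to a fuller document.

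**Conclusion.** The point holds in a limited form. As written, CV mortality leaves out sudden and arrhythmic deaths and has no clear place for valve-disease and valve-procedure deaths. This understates CV mortality by the omitted share, loses events, and shifts the AS hazard ratio when that share differs by AS status. The size and direction of the shift cannot be known from the documents: on the assumed rates a true ratio of 2.0 is recorded as anything from 1.78 to 2.25. If the hazard ratio is the same for all CV causes, the cost is events and power only, from 0.84 to between 0.80 and 0.70 under the stated assumptions.

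A related, smaller gap concerns CV events. A first occurrence that is a heart-failure death without admission, an aortic death or a sudden death is not a CV event. A fatal stroke outside hospital is unclear, because the admission condition may attach to stroke or only to peripheral artery disease. This calls for a supplementary analysis, not for replacing the endpoint.

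The definition should be corrected, but the defect does not threaten the study or its first-listed outcome.

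**What to change.** 1. Extend CV-related death to include sudden or arrhythmic death and death from valvular heart disease, including death from a valve procedure.
2. State whether aortic disease covers the aortic valve.
3. Keep sepsis linked to peripheral artery disease under infection-related death, as now.
4. Add these cause categories to the yearly questionnaire where it lacks them. The form is not shown, so some may already be there.
5. Keep the CV-event endpoint, state whether its admission condition applies to stroke, and report the time to first CV event or CV death as an additional analysis.

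The cost is revised wording, slightly more coding by the facilities and one added analysis. No extra visits or patients are needed. The change is best made before causes are coded, because categories that were not collected are hard to recover later.

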### Statistical processing

We will use SPSS statistics version 24 and the Easy R program [12] for statistical processing. Patient characteristics and baseline data will be compared between those with or without AS and those classified by AS stages using an unpaired t-test, analysis of variance for continuous variables, and Fisher’s exact test for nominal variables. We will compare incidence of all-cause mortality, CV events, CV-related mortality, infection-related mortality, and new onset of AS by using the log-rank test for Kaplan-Meier curves. The factors that contribute to all-cause mortality, CV events, CV-related mortality, infection-related mortality, and new onset of AS will be examined using univariate regression analysis. We will conduct multivariate Cox proportional hazards analysis using models with adjustment for some variables including age, gender, and factors that will be extracted as significant variables by univariate analysis. We will also examine factors contributing to annual change rates of mPG, AVA, and aortic Vmax with multiple regression analysis by using models. Continuous variables will be expressed as the mean and standard deviation, or the median and interquartile range, and categorical variables will be presented as a percentage. *P*-values less than 5% will be considered statistically significant.

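### Kaplan-Meier curves are set to show the incidence of four outcomes that death from another cause precludes, so the plotted incidence will be too high; the log-rank and Cox comparisons remain valid for cause-specific hazards

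*Protocol article*

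**What the plan says.** The Statistical processing section of the protocol article states what is to be compared and by which test: "We will compare incidence of all-cause mortality, CV events, CV-related mortality, infection-related mortality, and new onset of AS by using the log-rank test". The curves are named where that list ends: "new onset of AS by using the log-rank test for Kaplan-Meier curves". Regression follows: "We will conduct multivariate Cox proportional hazards analysis using models with adjustment for some variables including age, gender".

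The Outcomes section makes CV-related and infection-related mortality separate outcomes beside new onset of AS: "3) CV-related mortality rates, 4) infection-related mortality rates, and 5) new onset or development of AS". It defines CV death by a closed list of causes: "CV-related death is defined as death due to heart failure, acute coronary syndrome, aortic disease, or stroke". Its definition of CV events starts with events in a living patient: "CV events are defined as heart failure requiring hospitalization, acute coronary syndrome".

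The article as shown does not mention competing events, cumulative incidence functions, or cause-specific or subdistribution hazards. Nor does it say how a death from another cause is handled in the four outcomes other than all-cause mortality.

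**The concern.** The curves are named as the tool for comparing incidence. A patient who dies of infection can no longer die of a CV cause, and the reverse. A patient who dies of anything can no longer have a first CV event or develop AS. Kaplan-Meier with such deaths censored assumes that these patients would have gone on to the same risk as those still alive. The resulting curve describes a setting in which nobody dies of anything else, not the share of patients who actually have the event.

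The article gives reason to expect that this matters. Enrolment runs from July 2017 to June 2018 and follow-up ends in June 2023, so patients are followed for 5 to 6 years. The Treatment strategy section of the Discussion expects the results to inform treatment of dialysis patients with AS, and absolute risks are what a reader would take from the curves for that purpose.

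**Working it through.** **Is there a figure to reproduce?** No. The article gives no event rate, power or event count for these outcomes; the sample size of about 2400 is a count of consecutive cases. The check is therefore of the method, under assumed rates.

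**Inputs assumed, not in the documents.** Constant hazards; all-cause mortality 0.10 per year (range 0.06 to 0.14); 40% of deaths CV and 20% infection; new-onset AS 0.05 per year; horizon T = 5 years. The nearest figure in the article is a cited severe-AS series, not all on dialysis, with 167 of 519 dead at a median of 3.5 years. That is 32.2%, or -ln(1 - 0.322)/3.5 = about 0.11 per year. It shows that the assumed level is not far-fetched; it does not establish the rate in this cohort.

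**Formulas.** With event hazard l and total hazard h (event plus competing death):

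- 1 minus Kaplan-Meier, other deaths censored: 1 - exp(-lT)
- Actual cumulative incidence: (l/h) × (1 - exp(-hT))

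The first exceeds the second whenever h > l.

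**Central case, h = 0.10 for deaths.**

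- Infection death, l = 0.02: 1 - exp(-0.10) = 9.5%; 0.2 × (1 - exp(-0.5)) = 7.9%; ratio 1.21.
- CV death, l = 0.04: 1 - exp(-0.20) = 18.1%; 0.4 × 0.393 = 15.7%; ratio 1.15.
- New-onset AS, l = 0.05, h = 0.15: 1 - exp(-0.25) = 22.1%; (0.05/0.15) × (1 - exp(-0.75)) = 17.6%; ratio 1.26.

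**Range.**

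| All-cause mortality per year | CV death: 1-KM / actual (ratio) | Infection death: 1-KM / actual (ratio) | New AS: 1-KM / actual |
|---|---|---|---|
| 0.06 | 11.3% / 10.4% (1.09) | 5.8% / 5.2% (1.12) | 22.1% / 19.2% |
| 0.10 | 18.1% / 15.7% (1.15) | 9.5% / 7.9% (1.21) | 22.1% / 17.6% |
| 0.14 | 24.4% / 20.1% (1.21) | 13.1% / 10.1% (1.30) | 22.1% / 16.1% |

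For CV events, with event hazards of 0.03 to 0.10 and competing death of 0.04 to 0.11 per year (also assumed), the 5-year ratio is 1.09 to 1.29.

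**Does it distort AS against no AS?** Take the central case for no AS; gaps are from unrounded values.

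- *AS doubles CV death only* (l = 0.08, h = 0.14). CV death with AS: 33.0% by 1-KM, 28.8% actual, ratio 1.15, the same as without AS. The AS/no-AS risk ratio is 1.82 by 1-KM and 1.83 actual. The gap is 14.8 points against 13.0. For infection death, both 1-KM curves read 9.5%, while actual risks are 7.2% (AS) and 7.9% (no AS).
- *AS doubles every cause* (CV l = 0.08, h = 0.20). CV death with AS: 33.0% by 1-KM, 0.4 × (1 - exp(-1)) = 25.3% actual, ratio 1.30. The risk ratio is 1.82 by 1-KM and 1.61 actual; the gap is 14.8 points against 9.5.

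**Does the log-rank test fail?** A simulation of 2000 trials, N = 2400 with an assumed 20% AS, gave both groups the same infection-death hazard and doubled the competing hazard in AS. The test rejected in 4.9% of runs, so it keeps its 5% level for cause-specific hazards.

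**The case against.** Four objections deserve an answer.

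1. *The tests are valid.* A reader might infer that log-rank and Cox are wrong for the four outcomes. They are not. With other deaths censored, both compare cause-specific hazards, which is a legitimate target when the question is whether AS is associated with an outcome, and the Outcomes section speaks of mortality rates. Nor does censoring leave the dead at risk; it removes them. This objection stands in full and confines the fault to the curves and to reading them as incidence.

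2. *The bias need not be worst in AS patients.* A reader might infer that the AS group is always the most overstated and its contrast with no AS always distorted. The documents only hypothesise poorer outcomes with AS. A larger relative bias requires AS to raise the competing deaths. If AS raises only CV death, the CV-death ratio is almost unchanged and only the absolute gap is inflated. For new-onset AS the comparison by baseline AS does not exist, since patients with AS cannot newly develop it. This also stands.

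3. *Gray's test is not a correction of log-rank.* With equal infection hazards, cumulative incidence shows a lower infection-death risk in AS (7.2% against 7.9%) merely because more patients die first of CV causes. Testing that answers a different question. This stands, so Gray's test should be optional.

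4. *The article is condensed and does not say 1-KM values will be reported as risk.* This stands in part. Handling of other deaths is not stated, and an analysis plan may settle it. But the article does fix the curves and calls the quantity incidence, which is a stated choice and not a silence.

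**Conclusion.** The point holds in limited form. Kaplan-Meier curves are the wrong display of incidence for CV events, CV death, infection death and new-onset AS. With competing deaths censored, the overstatement is certain in direction. Under the assumed rates it is about 9-21% relative for CV death and 12-30% for infection death at 5 years, and about 3 to 6 points for new-onset AS (22.1 - 19.2 = 2.9; 22.1 - 16.1 = 6.0). These sizes rest on constant hazards and on mortality and cause shares that the article does not give.

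Distortion of the AS contrast is conditional: on the absolute scale about 15 against 13 points if AS doubles CV death only, and on both scales if AS also raises competing deaths.

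All-cause mortality, the first-listed outcome and the centre of the stated aim, is unaffected, and the planned tests and hazard ratios remain interpretable. This should be fixed before the outcome papers are written; it does not undermine the study.

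**What to change.** In Statistical processing:

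- Keep Kaplan-Meier and log-rank for all-cause mortality.
- For CV-related and infection-related death, show Aalen-Johansen cumulative incidence with death from any other cause as the competing event.
- For CV events and new-onset AS, do the same with any death before the event as the competing event.
- Keep log-rank and Cox for these four outcomes, and state that they compare cause-specific hazards.
- Offer Gray's test or a Fine-Gray model as an optional secondary analysis where absolute risk is the question.

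The cost is about two sentences and a little more analysis work. No new data are needed: the Follow-up schedule already collects survival, CV event categories, onset dates and clinical outcomes, and cause of death is needed anyway to classify CV-related and infection-related deaths. The reported incidences will be somewhat lower.

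### Hypothesis 5 claims that outcomes worsen across AS stages, but the only test named for comparing outcome incidence, the log-rank test, ignores stage order in its ordinary four-group form

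*Protocol article*

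**What the plan says.** The Backgrounds section lists five hypotheses. The fourth contrasts patients with and without AS. The fifth is a separate claim about a gradient: "Outcomes are poorer according to AS stages".

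Under Definition and classification of AS, the article says "We will evaluate stages A to D of AS according to the AHA/ACC Guideline". It then plans to compare outcomes, including all-cause mortality and CV events, between patients with and without AS and among "4 groups by stages".

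Under Statistical processing, mortality (all-cause, CV-related and infection-related), CV events and new onset of AS are to be compared "by using the log-rank test for Kaplan-Meier curves". Regression is planned alongside: "We will conduct multivariate Cox proportional hazards analysis using models with adjustment for some variables". Its stated purpose is to find factors that contribute to each outcome, and the adjustment set is age, gender and whatever is significant in univariate analysis. AS stage, its coding and an ordered contrast are not mentioned there. The significance level is 5%.

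**The concern.** An ordered hypothesis is paired with a test that does not use the order. Unless a trend version is named, a log-rank test on four groups asks only whether the four hazards are all equal. It can reject when one middle stage is worse than the rest, and its p-value would be the same if the earliest stage fared worst.

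Two things are at stake. First, a p-value below 5% could be reported as support for hypothesis 5 when it shows only that the stages differ somehow. Second, if the gradient is real and roughly even, spreading the test over 3 degrees of freedom makes it easier to miss. The sample size was set by one year's accrual and not by a power calculation, so no planned margin is known to absorb that loss.

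**Working it through.** The Sample size section gives no power, effect size, event count or stage distribution, so the plan has no figure of its own to reproduce. The check is in three parts.

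**1. Does the test ignore order?** One data set was simulated with 2400 patients, stage shares of 70/20/7/3%, a hazard of 0.08 per year in the first stage multiplied by 1.2 per stage, and censoring at 5 years. The four-group log-rank statistic was 27.897 on 3 df. After the stage labels were rearranged it was again 27.897.

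**2. Power under a log-linear gradient, free of study-specific assumptions.** If the log hazard rises by an equal amount per stage, the 1-df trend test and the 3-df test have the same non-centrality λ and differ only in degrees of freedom. Two-sided alpha is 0.05.

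- Trend test, 80% power: λ = (1.960 + 0.842)² = 7.85. A 3-df chi-square test at λ = 7.85 has power 64.5%.
- Trend test, 90% power: λ = 10.51. The 3-df test then has power 78.4%.
- For 80% power the 3-df test needs λ = 10.90, and 10.90 / 7.85 = 1.39.
- For 90% power it needs λ = 14.17, and 14.17 / 10.51 = 1.35.

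Since λ is proportional to events, the 3-df test needs 35 to 39% more events.

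**3. What this could mean here, under assumed inputs.** The article's 2400 patients are used. Everything else is assumed: stage shares p of 70/20/7/3%, 5 years of follow-up, and annual mortality of 5% or 10%. Deaths are D = 2400 × (1 − 0.95⁵) = 543, or D = 2400 × (1 − 0.90⁵) = 983. With β the log hazard ratio by stage, stage scores s = 0, 1, 2, 3, and event shares taken as patient shares:

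- 3-df test: λ = D × Σp(β − β̄)²
- trend test: λ = D × [Σp(s − s̄)(β − β̄)]² / Σp(s − s̄)²

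Example: s̄ = 0.20 + 0.14 + 0.09 = 0.43, and Σp(s − s̄)² = 0.75 − 0.43² = 0.565. For a hazard ratio of 1.15 per stage and 543 deaths, both tests have λ = 543 × 0.565 × (ln 1.15)² = 5.99. Power is 68.7% on 1 df and 51.8% on 3 df.

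| Deaths | Hazard ratios, stages A to D | Trend, 1 df | Unordered, 3 df |
|---|---|---|---|
| 543 | 1.15 per stage | 68.7% | 51.8% |
| 543 | 1.20 per stage | 89.1% | 77.0% |
| 543 | 1.30 per stage | 99.6% | 98.1% |
| 983 | 1.10 per stage | 61.3% | 44.4% |
| 983 | 1.15 per stage | 90.9% | 79.8% |
| 543 | 1, 1.3, 1.3, 1.3 | 68.7% | 64.5% |
| 543 | 1, 1, 1, 2 | 38.1% | 62.9% |
| 543 | 1, 1.6, 1, 1 | 38.3% | 96.9% |
| 543 | 1, 1.5, 1, 2 | 87.1% | 97.5% |

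In the first five rows the trend test gains up to about 17 percentage points at moderate power and almost nothing when the gradient is strong. The sixth row is close, and the last three favour the unordered test. The row 1, 1.6, 1, 1 shows the unordered test almost certain to reject with no gradient present. The last row shows that a trend test can also reject often when the stages are not strictly ordered.

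**The case against.** The strongest reply is that this is a condensed article. It does not call the log-rank test unordered, and its log-rank sentence does not mention stages. The choice of a trend version or of stage coding is often left to an analysis plan, which is not shown. This lowers the severity but does not remove the point: the article names a test for outcome comparisons, elsewhere makes stage one of those comparisons, and the named test in its ordinary form does not match the hypothesis. The point rests on what is named, not on silence.

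A reader might infer that the planned analysis cannot show any ordering. The article does not support that. Four Kaplan-Meier curves display direction, and the Cox analysis could give stage-specific hazard ratios if stage is entered. These would be descriptive, and the article does not commit to them as the test of hypothesis 5.

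A reader might also infer that the log-rank test loses power generally, or loses more when the higher stages are small. Neither follows. The loss depends on the pattern, and hypothesis 5 does not say that the steps between stages are equal. Under a log-linear gradient, small stages lower λ equally for both tests, so the 1.35 to 1.39 event ratio does not depend on stage shares. Where only a 3% last stage differs, the trend test is the weaker one.

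Finally, the analysis of variance also ignores order, but the article uses it for baseline characteristics. Hypothesis 5 concerns outcomes, so it has no bearing here.

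**Conclusion.** The point holds in limited form. The only between-group test named for outcome incidence does not, in its ordinary four-group form, address the ordered claim of hypothesis 5, so a significant result would not by itself support that claim. Under a roughly log-linear gradient over equally spaced stages, power is about 64% against 80%, or 78% against 90%. For other patterns the difference can vanish or reverse. The study-specific power figures rest on assumed stage shares, mortality and hazard ratios, none of which the article gives. No figure in the article is wrong, the study is observational and hypothesis 5 is one of five, so severity is minor to moderate.

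**What to change.** In Statistical processing, state that hypothesis 5 is tested with a log-rank test for trend across stages A to D, or with an ordinal stage term in the adjusted Cox model. Keep the unordered log-rank test. Report stage-specific hazard ratios with confidence intervals and a check for departure from linearity, since a significant trend alone does not establish that each stage is worse than the one before.

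The cost is one or two sentences and no new data. The drawback is that a trend test is less sensitive to patterns that are not graded, which the retained unordered comparison covers. The choice should be recorded before the final data are fixed (31 December 2023 in Table 1), so that it is not made after seeing the curves.
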